**Fig. 1 Fig1:**
[figure not shown]
Flow chart of the prospective cohort study

##### Questionnaire

The baseline questionnaire has five sections: the first section covers socio-demographic characteristics, section two is on pregnancy and fertility preferences, section three is on contraception services received, section four is on the perception of the quality of care received at the health facility, and the section five is on the decision-making environment. From the pilot study conducted, we anticipate initial data collection to take 20–25 min. The follow-up questionnaires are shorter with only two sections; the first section is on contraceptive history. Participants will be asked whether they are still using their baseline contraception method, any side effects and or complications experienced, and the level of satisfaction with the method. The second section will be for clients reporting discontinuation or contraceptive switching, both closed- and open-ended questions on the timing and reasons for discontinuation or switching, including fertility intention, will be asked.

##### Sample size

This phase is powered to detect a 10 percentage point difference in the primary outcome of interest— reductions in contraceptive discontinuation rates at 12 months, between baseline and endline levels with a 95% confidence interval and a power of 80%. For the purpose of the sample size calculation, Kenya DHS data was used for the current contraceptive discontinuation rate of 31% [9]. Further, the sample size is adjusted to account for a 30% attrition rate due to potential dropouts and loss of clients during follow-up through the four waves of data collection up to 24 months and a design of effect of 1.5 due to cluster sampling. This results in a total sample size of 508, which is doubled for the overall study (for the two counties), leading to 1016 women. Proportionate to size is used to allocate the sample size for each of the 10 facilities based on the current family planning caseload. Additionally, the current method mix for the two counties further determines the sample for each modern contraceptive method.

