### Study design

This single group longitudinal study is being implemented in two phases employing multiple designs to respond to the objectives.

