#### Phase 2: evaluation of the prospective cohort

A prospective cohort design will be utilized in this phase among women initiating family planning services in 10 study sites in Kenya.

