##### Dissemination of study findings

The study team plans to disseminate findings among national and sub-national stakeholders through in-country dissemination events to demonstrate how, with a focus on quality in family planning, the level of satisfaction and discontinuation rate have changed. The results will be published in peer-reviewed journals and presented at both national and international conferences. Briefs indicating policy and programmatic implications will be developed and shared with the government and other stakeholders. The study will contribute to the body of knowledge that will inform decision-makers locally and globally on the determinants of contraceptive discontinuation and couple-level decision-making on the same.

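### The stated 80% power is for a baseline-to-endline reduction, but the single post-intervention cohort has no internal baseline rate and no planned analysis compares it with the external 31%

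*Protocol article*

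**What the plan says.** All references are to the protocol article.

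- **Sample size:** "This phase is powered to detect a 10 percentage point difference in the primary outcome of interest", described as "reductions in contraceptive discontinuation rates at 12 months, between baseline and endline levels with a 95% confidence interval and a power of 80" percent. The starting rate is external: "Kenya DHS data was used for the current contraceptive discontinuation rate of 31" percent. Two inflation factors follow: "the sample size is adjusted to account for a 30% attrition rate" and "a design of effect of 1.5 due to cluster sampling". The result is 508, doubled to 1016 because there are two counties.
- **Study design:** "This single group longitudinal study is being implemented in two phases".
- **Phase 2, evaluation of the prospective cohort:** "A prospective cohort design will be utilized in this phase among women initiating family planning services". The abstract's Methods paragraph places this cohort after implementation of the intervention in the 10 facilities.
- **Outcomes:** the primary outcome is a single quantity, the discontinuation rate at 12 months. A woman has discontinued when she reports at follow-up that she no longer uses her baseline method.
- **Participant follow-up:** the 12- and 24-month time points are said to permit comparison with other surveys, including the DHS. No hypothesis or test is attached.
- **Data analysis (Phase 2):** descriptive statistics, tests of continuers against discontinuers, Kaplan-Meier rates, and a Cox model for predictors.
- **Dissemination of study findings:** the results are intended "to demonstrate how, with a focus on quality in family planning, the level of satisfaction and discontinuation rate have changed".

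**The concern.** Three parts of the article describe three different questions. The sample size section powers a reduction between two levels. The outcomes and analysis sections estimate one level. The dissemination section promises a demonstrated change.

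Only one of the two levels comes from the study. Every woman enters on her baseline method and after the intervention has begun, and no pre-intervention cohort or control facility is described. The other level can only be the DHS figure, which enters as a planning input and is not named as a comparator in any analysis.

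The 80% power is therefore quoted for a contrast the design does not contain. If nothing is changed, the powered question may go unanswered, or a before/after claim may be put together once the data are in. A single post-intervention group set informally against a national survey cannot support such a claim, and the results are meant to inform policy.

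**Working it through.** **Inputs (Sample size section):** reference rate 31%; reduction of 10 points, so 21%; 95% confidence; power 80%; design effect 1.5; attrition 30%; 508 per county; 1016 in total. Sidedness and formula are not stated.

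**1. Reproducing 508.** Two independent proportions, pooled variance under the null, mean rate 0.26:

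n per group = [z_α √(2 × 0.26 × 0.74) + 0.8416 √(0.31 × 0.69 + 0.21 × 0.79)]² / 0.10²

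| Calculation | n before inflation | × 1.5 / 0.7 |
|---|---|---|
| Two-sample, one-sided 5% (z_α = 1.645) | 237 per group | 507.9, i.e. 508 |
| Two-sample, two-sided 5% (z_α = 1.960) | 301 per group | 645 |
| One sample against fixed 31%, two-sided | 156.1 | about 335 |
| One sample against fixed 31%, one-sided | 121.8 | about 261 |

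Only the first row gives 508. It is the size of one of two equal groups. The doubling to 1016 is explained by the two counties, so it does not supply the second group. On this formula, 508 per group gives about 70% power for a two-sided test.

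**2. What the planned cohort can deliver.** With the plan's own factors:

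- Effective n per county = 508 × 0.7 / 1.5 = 237.1. Pooled = 1016 × 0.7 / 1.5 = 474.1.
- 95% CI half-width at 31% = 1.96 × √(0.31 × 0.69 / n): 5.9 points per county, 4.2 pooled. At 21% it is 5.2 and 3.7.
- Two-sided power against a fixed 31% when the truth is 21%, per county: Φ[(0.10 − 1.96 × 0.0300) / 0.0265] = Φ(1.55) = 0.94. Pooled: Φ[(0.10 − 1.96 × 0.0212) / 0.0187] = Φ(3.12) = 0.999.
- Smallest reduction detectable with 80% power: about 8.2 points per county and 5.8 pooled.

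**3. Why these are upper-end figures.**

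- *Few clusters.* There are 10 facilities. The split by county is not given. If it is five each, a t reference with 4 degrees of freedom (2.776) widens the county half-width to 2.776 × 0.0300 = 8.3 points. Power, from a noncentral t with the standard error at 21% (0.10 / 0.0265 = 3.78), falls to about 80%. Pooled with 9 degrees of freedom (2.262), the half-width is 2.262 × 0.0212 = 4.8 points.
- *DHS sampling error.* The documents give none. As an assumed range, a standard error of 1 to 2 points added in quadrature to both standard errors lowers county power from 94% to between 91% and 81%, and pooled power from 99.9% to between 99% and 94%, before any small-cluster correction.

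One input works the other way. The 30% attrition covers loss up to 24 months, and women lost later still contribute to a 12-month Kaplan-Meier estimate. The effective n at 12 months may therefore be larger, by an amount the article does not allow one to calculate.

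**4. Looking for the comparison.** None of the analyses listed in the Phase 2 Data analysis section sets the 12-month rate against another rate. The only group comparison is between continuers and discontinuers within the cohort.

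**The case against.** The best defence is that baseline means the DHS rate and endline means the cohort's 12-month rate. The sample size section calls the DHS figure the current rate, and the follow-up section mentions comparability with the DHS. That is the natural reading, and on it there is no shortage of women: about 335 per county would suffice against a fixed 31%, and 508 are planned. It can be added that the exact test is often left to an analysis plan not shown here, and that none of the stated objectives is a hypothesis of change.

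Much of this stands. It rules out two stronger readings that a reader might infer:

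- *That the primary outcome cannot be obtained.* The primary outcome is one 12-month rate, the second objective is to determine rates, and Kaplan-Meier estimation provides them.
- *That the baseline group has zero observations, so the comparison is empty.* This assumes an internal baseline, which is the less plausible reading of the text.

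Two things remain. First, if the DHS rate is the comparator, the quoted 80% is not the power of that comparison, and 508 does not come from it. Second, an analysis plan can specify a test, but it cannot supply a pre-intervention group, and the wording on power and dissemination is already fixed in the article. The two-sample, one-sided origin of 508 is inferred, because the article names no formula, although the match is exact after rounding up.

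**Conclusion.** The point holds as a mismatch between the powered contrast and the design. The 80% power refers to a two-group reduction, while the study has one post-intervention group and an external reference that no listed analysis uses. The estimate of the primary outcome is not at risk. What lacks support is the stated power and any claim that the rate has changed because of the intervention.

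For the study as designed, the attainable precision is about ±5.9 points per county and ±4.2 pooled at 31%, with about 94% power per county against a fixed 31%. These figures assume the plan's design effect and attrition, a known reference rate and a normal approximation. They worsen with few facilities and with DHS sampling error.

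A DHS comparison would also be between differently selected populations. The eligibility section excludes users of condoms, emergency contraception and surgical methods, non-residents, women without a phone they control, those unwilling to be followed for 24 months, and those planning pregnancy.

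**What to change.** Keep 1016 women and make three changes.

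1. **Sample size.** Replace the baseline-to-endline contrast with either estimation of the 12-month rate or a pre-specified two-sided comparison with the external DHS rate. Restate precision or power for that choice. Make the pooled analysis primary, with a small-cluster correction for 10 facilities, and report the counties as secondary. If the DHS comparison is chosen, include the survey's sampling error.
2. **Data analysis (Phase 2).** Add the 12-month Kaplan-Meier estimate with a facility-clustered 95% CI, and the comparison if one is made. Where possible, restrict or standardise the DHS reference to the methods eligible for the cohort, and state the selection differences that remain.
3. **Dissemination.** Report the discontinuation rate as compared with the external DHS rate, without attributing a difference to the intervention. Satisfaction is among the data listed for the five time points, so its course over follow-up within the cohort may be described, but not as a change from before the intervention.

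The cost is revised wording, one extra analysis and a more modest conclusion. No participants are added. A true before/after contrast would need a second cohort: on the plan's one-sided formula 508 per cohort per county, or 2032 overall (508 × 2 × 2), and with a two-sided test 645, or 2580 overall.

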## Methods

### Study setting

The study will be implemented in 10 sites, both public and private health facilities in Migori and Kitui counties in Kenya. Migori is in southwestern Kenya, 368 km from Nairobi, Kenya’s capital, and borders Tanzania to the west. Kitui is 170 km south-east of Nairobi. Kenya’s population is estimated to be 51 million people, Migori and Kitui counties have a population of 1.1 million each. The total fertility rate for Migori and Kitui counties is 5.3 and 3.9 respectively [9]. As per the last Kenya DHS of 2014, the mCPR for Kitui County was 55%, two percentage points higher than the national average; the recent PMA 2020 data of 2018 indicated an improvement to 63% [9, 10]. Migori’s 2014 mCPR was 44%, nine percentage points lower than the national average [9]. The two counties have a diverse method mix; Migori’s mCPR is mostly driven by long-acting reversible contraceptives, at 72%. In Kitui, short-term methods are more popular, at 64%. While there is no ideal method mix, the study will explore the dynamics and drivers of contraceptive use in the two counties, which have a varied method mix, to assess how they influence discontinuation or continuation.

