##### Study population and eligibility criteria

Women of reproductive age, 15 to 49 years initiating family planning services in 10 health facilities in Kitui and Migori counties are eligible to participate. All enrolled individuals will be invited for follow-up interviews at 3, 6, 12, and 24 months. The following will be excluded from participation in this study: women who take up condoms, emergency contraception, or voluntary surgical contraception; are not residents of the selected study region; women do not have access to a phone they can control for ease of follow-up and are not willing to be followed up for a period of 24 months with four contacts; and women who are planning to get pregnant within the study duration.

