##### Participant follow-up

Participants will be enrolled for 24 months. Data on current method use, side effects and complications, fertility intentions, satisfaction, motivation, and decision-making, including male partner involvement on contraceptive use, will be collected at five different points in time to assess the dynamics of contraceptive use, either continuation, discontinuation, or switching. Data collection will occur the following time points: at baseline and at 3, 6, 12, and 24 months (Fig. 1). At baseline, individuals who are eligible to participate and have consented to be part of the study, will complete an online questionnaire, which will be more extensive (the questionnaire is described in more detail below), prior to leaving the health facility. Participants will provide their phone contact information to enable the research team to get in touch in the subsequent follow-up period for brief interview sessions. During each follow-up interview, consent will be sought to ensure the participants are still interested in participating in the study. During each round of follow-up interviews, three attempts will be made to contact participants before a determination of loss to follow-up is made. The second and third round of interviews will take place at 3 and 6 months after baseline, because women who choose some short-term methods will require a 3-month cycle for resupply. The follow-up at 12 months will be used to determine the contraceptive continuation rate, which is the primary outcome for this study. The 12 and 24 months’ period allows comparisons with other surveys, including the DHS, that have used the same time reference to report discontinuation.

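### The Kenya DHS rate of 31% is the only numeric reference for the reduction the study wants to show, but it is not matched to this selected, single-group cohort

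*Protocol article*

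**What the plan says.** The Study design section describes a single-group longitudinal study. Under Sample size, "This phase is powered to detect a 10 percentage point difference in the primary outcome of interest", namely a reduction in 12-month discontinuation "between baseline and endline levels with a 95% confidence interval and a power of 80" per cent. The starting level is taken from a survey: "Kenya DHS data was used for the current contraceptive discontinuation rate of 31" per cent. With 30% attrition and a design effect of 1.5 this leads to 508 women, doubled to 1016 for the two counties.

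The eligibility section excludes "women who take up condoms, emergency contraception, or voluntary surgical contraception" and "women who are planning to get pregnant within the study duration". It also excludes non-residents, women without a phone they control and women unwilling to be followed for 24 months. Within the sample, "the current method mix for the two counties further determines the sample for each modern contraceptive method". Study setting describes Migori's contraceptive prevalence as "mostly driven by long-acting reversible contraceptives, at 72" per cent and gives short-term methods 64% in Kitui.

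Participant follow-up says that the 12- and 24-month time points make the study one that "allows comparisons with other surveys, including the DHS, that have used the same time reference to report discontinuation". The dissemination section plans to show how discontinuation has changed with the focus on quality. The Phase 2 Data analysis section plans Kaplan-Meier rates and Cox models.

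**The concern.** A cohort of initiators cannot supply its own baseline 12-month discontinuation rate, and no pre-intervention or comparison cohort is described. The 31% is therefore the only numeric baseline in the article, and any statement that discontinuation fell would have to lean on it.

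Sharing a 12-month window aligns the time scale but not the women. The same figure is used for two counties with opposite method mixes, and for a cohort restricted by method, fertility intention, phone access and willingness to be followed. If these features alone put the untreated rate below 31%, the study could report a programme benefit that is really a difference in case mix.

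**Working it through.** **1. The plan's own figure.** Inputs from Sample size: 31% against 21%, power 80%, design effect 1.5, attrition 30%. The two-sample formula for proportions with a one-sided 5% test gives

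n = [1.645·√(2·0.26·0.74) + 0.842·√(0.31·0.69 + 0.21·0.79)]² / 0.10² = 237 per group.

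Then 237 × 1.5 / 0.70 = 507.9, that is 508, so the stated figure is reproduced. (A two-sided 5% test gives 301 per group, and 301 × 1.5 / 0.70 = 645.) This confirms that 31% serves as the baseline level of the planned difference.

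**2. Method mix alone, no intervention effect.** The shares come from Study setting. Everything that is not short-term in Kitui is taken as long-acting (100 − 64 = 36%), and everything that is not long-acting in Migori as short-term (28%). The 12-month rates by method are assumptions, because the article gives none. With L the long-acting and S the short-term rate:

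- Migori = 0.72·L + 0.28·S
- Kitui = 0.36·L + 0.64·S
- Overall = the mean of the two (508 women each)

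| L / S (assumed) | Migori | Kitui | Overall | Overall minus 31 |
|---|---|---|---|---|
| 10% / 40% | 18.4% | 29.2% | 23.8% | −7.2 |
| 10% / 45% | 19.8% | 32.4% | 26.1% | −4.9 |
| 15% / 40% | 22.0% | 31.0% | 26.5% | −4.5 |
| 15% / 45% | 23.4% | 34.2% | 28.8% | −2.2 |

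Migori lies 7.6 to 12.6 points below 31%, and reaches 10 points only when L is 10%. Kitui lies on both sides of 31%. A wider assumed grid (L 5 to 12%, S 35 to 45%) gives Migori 13 to 21%, Kitui 24 to 33% and overall 19 to 27%. Ten points overall is reached only in the low corner of that grid.

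**3. Exclusions alone.** Assume that condom users are 2 to 8% of the reference and stop at 40 to 60%, that surgical users are 0 to 6% and never stop, and that 1 to 5 points of the 31% are stops for wanting pregnancy. The restricted rate is (0.31 − condom share × condom rate − pregnancy points) / (1 − condom share − surgical share).

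- Lowest: (0.31 − 0.08·0.60 − 0.05) / 0.92 = 23.0%
- Highest: (0.31 − 0.02·0.40 − 0.01) / 0.92 = 31.7%

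The shift is −8.0 to +0.7 points: mostly downward, but not certainly so.

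**4. What a mismatch would do.** The effective sample is 508 × 0.70 / 1.5 = 237 per county and 474 overall. Against a fixed 31% with a two-sided 5% test, an observed rate is significantly lower at or below 0.31 − 1.96·√(0.31·0.69/237) = 25.1% per county, and at or below 26.8% overall. The chance of a significant reduction with no intervention effect is:

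| Untreated rate | Per county | Overall |
|---|---|---|
| 31% | 2.5% | 2.5% |
| 28% | 16% | 29% |
| 26% | 38% | 66% |
| 25% | 52% | 82% |

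With the one-sided 5% test that reproduces 508, the 26% row becomes 51% and 77%. If the reference is treated as an estimate from a sample of the same effective size, the per-county figure in that row is 22.5% (two-sided). All four Migori values in step 2 lie below 25.1%. None of the Kitui values does.

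**The case against.** A reader might infer that the exclusions and the method allocation lower discontinuation as a matter of fact, so that the full 10-point reduction would appear with no effect. The documents do not support that.

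- The 31% is introduced for the sample size calculation. Data analysis specifies no test against it, objective 2 is to determine rates, and the primary outcome is the rate itself. The comparison is implied by Sample size, Participant follow-up and the dissemination section, and is not laid down as a test. Other surveys are also mentioned as comparators, though without a figure.
- Not every exclusion acts downward. Removing surgical users raises the rate relative to an all-method reference. The effect of phone access and willingness to be followed is unknown.
- The county mix does not lower the rate everywhere. Kitui is mainly short-term, and the article gives neither the national mix nor method-specific rates.
- It is tempting to say that the allocation over-represents long-duration methods because it mirrors prevalent users. The article does not define its current method mix that way, and the preceding sentence concerns facility caseload.
- The Discussion notes that DHS calendar data are prone to recall bias. If short episodes are missed, a prospective cohort would record more discontinuation than the survey, which offsets some of the shift.
- Standardisation is often left to an analysis plan, which is not shown.

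All of this stands as a limit on direction and size. It does not make the 31% like-for-like. The reference rate, the exclusions and the allocation are all fixed in the article, and so is the aim of showing a reduction.

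**Conclusion.** The point holds in a limited form. The unadjusted 31% is the only numeric reference for the intended reduction, and the cohort differs from it by design. The net shift is probably downward and is most plausible in Migori. In Kitui it is not shown.

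Under the first set of assumed rates, mix alone puts the overall untreated rate about 2 to 7 points below 31%. A 10-point drop is within reach in Migori only at the lower long-acting rate. These sizes rest on assumed method-specific rates and on reading the Study setting shares as the enrolled mix. Even a 5-point mismatch matters, because it raises the chance of a falsely significant reduction from 2.5% to 38% per county and 66% overall when 31% is treated as fixed.

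**What to change.** For any comparison or claim of change, replace the flat 31% with a reference computed from DHS calendar episodes:

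- restricted to the methods eligible for the cohort;
- with stops for wanting pregnancy removed or censored;
- with the cohort's own rule for switching;
- standardised to the enrolled method (and age) distribution within each county.

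Report method-specific 12-month rates beside it. If the survey cannot support this, report the 12-month rate descriptively and claim no reduction.

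The cost is a secondary analysis of a survey already cited and a few sentences of analysis text. The downside is a wider interval on the county-level reference. Whether the survey holds enough episodes per county and method cannot be judged from the article. No extra participants and no change to the recruitment quotas are needed.

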##### Data analysis

Quantitative data will be collected on RedCap [17] and cleaned before analysis to ensure completeness. Descriptive analysis of quantitative variables will be done using measures of central tendency (mean, median) and measures of dispersion (range, standard deviation), as appropriate. Descriptive statistics will be used to assess contraceptive discontinuation, including switching. Pearson’s χ2 or t test, where appropriate, will be used for univariate analyses to compare characteristics of women who continued and discontinued their initial contraceptive method. Multivariate analysis will be implemented for variables that will be significantly associated with contraceptive continuation at bivariate analysis. The time to event for this survival analysis will be calculate from method initiation to the time point when the participant reports discontinuation with her baseline method. Censoring will be done for clients lost to follow-up and those reporting discontinuation of their baseline method. Contraceptive discontinuation rates will be calculated using the Kaplan Meier survival function. Cox proportional hazard regression model will be used to estimate hazard ratio for risk of contraceptive discontinuation for independent predictors of discontinuation. The level of significance will be set at a *p*-value < 0.05. For qualitative data, the approach for data analysis will be similar to what has been presented above under the formative assessment.

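### The sample size of 508 fits the two-group formula only at one-sided 5%, although the plan states 95% confidence; sidedness, comparison and matching power need restating

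*Protocol article*

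**What the plan says.** The Sample size section of the protocol article (Phase 2) opens: "This phase is powered to detect a 10 percentage point difference in the primary outcome of interest". It describes this outcome as "reductions in contraceptive discontinuation rates at 12 months, between baseline and endline levels", "with a 95% confidence interval and a power of 80" per cent. For the reference level, "Kenya DHS data was used for the current contraceptive discontinuation rate of 31" per cent. It then says that "the sample size is adjusted to account for a 30% attrition rate", applies a design effect of 1.5 for cluster sampling, and ends: "This results in a total sample size of 508, which is doubled for the overall study (for the two counties), leading to 1016 women".

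The Phase 2 Data analysis section adds: "The level of significance will be set at a *p*-value < 0.05". Neither section writes one-sided or two-sided, and neither names the sample size formula. The Study design section describes a single-group longitudinal study.

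**The concern.** A reader who sees 95% confidence, 80% power and a 0.05 threshold will assume a two-sided 5% test. If 508 was obtained with a one-sided critical value, the stated power does not belong to the test that the reader has in mind.

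The comparison raises a second question. A two-proportion formula returns the size of each of two groups. The article calls 508 a total, and its doubling to 1016 is for the two counties, not for a second group. The formula that appears to have been used, the single-cohort design and the wording therefore do not agree on what is compared with what.

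At stake is how the primary result at 12 months will be read. A non-significant finding would be judged against an 80% figure whose test and comparison the article does not identify.

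**Working it through.** **Inputs, all from the Sample size section.** Reference p0 = 0.31; target p1 = 0.31 − 0.10 = 0.21; power 80% (z = 0.8416); design effect 1.5; attrition 30%. The level is 5%, with z = 1.6449 one-sided or 1.9600 two-sided. The mean proportion is 0.26.

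**Formula.** Size per group for two independent proportions, pooled variance under the null:

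n = [zα·√(2 × 0.26 × 0.74) + zβ·√(0.31 × 0.69 + 0.21 × 0.79)]² / 0.10²

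The two square roots are √0.3848 = 0.6203 and √0.3798 = 0.6163.

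**Reproducing 508 (one-sided 5%).** n = (1.6449 × 0.6203 + 0.8416 × 0.6163)² / 0.01 = 236.9. Then 236.9 × 1.5 / 0.70 = 507.5, which rounds up to 508.

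**Same formula, two-sided 5%.** n = (1.9600 × 0.6203 + 0.8416 × 0.6163)² / 0.01 = 300.8. Then 300.8 × 1.5 / 0.70 = 644.7, which rounds up to 645.

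**Other formulas.**
- One-sided, with × 1.5 / 0.70: unpooled variance 503, average variance 510, arcsine 506. All lie close to 508.
- Two-sided: unpooled 639; attrition applied as × 1.3 instead of / 0.70, 587; continuity-corrected 688. None is close.
- A few unusual two-sided routes do land near 508. Variance 2 × 0.31 × 0.69 with no attrition allowance gives 504. A one-sample formula using the 21% variance, × 1.5 × 1.3 and an extra doubling, gives 508. Each drops a stated adjustment or adds an unstated one.

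**Power of the two-group contrast.** With 508 enrolled per group, the effective size is 508 × 0.70 / 1.5 = 237, and 0.10 × √237.07 = 1.5397.
- One-sided: (1.5397 − 1.6449 × 0.6203) / 0.6163 = 0.843, power 80.0%.
- Two-sided: (1.5397 − 1.9600 × 0.6203) / 0.6163 = 0.526, power 70.0%.
- Two-sided with 1016 per group: effective size 1016 × 0.70 / 1.5 = 474, power 94%.

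**Power of the one cohort against 31% taken as fixed, two-sided 5%.** Power = Φ[(0.10·√n − 1.9600·√(0.31 × 0.69)) / √(0.21 × 0.79)], where the roots are 0.4625 and 0.4073.
- One county (n = 237): (1.5397 − 0.9065) / 0.4073 = 1.555, power 94%.
- All 1016 (n = 474): (2.1775 − 0.9065) / 0.4073 = 3.12, power 99.9%.

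| Comparison, two-sided 5% | 508 | 1016 |
|---|---|---|
| Two groups of this size each | 70% | 94% |
| One cohort against fixed 31% | 94% | 99.9% |

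The survey's effective sample size is not given in the article. The two rows bracket the answer: an equally large reference sample at one end, a reference without sampling error at the other.

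**The case against.** The strongest reply has three parts.

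First, the plan never writes two-sided. Its aim is directional, a reduction, and at one-sided 5% the figure of 508 is correct for 80% power. This stands as far as it goes: two-sided is an inference from the confidence level and the 0.05 threshold. But a one-sided 5% test corresponds to a 90% two-sided interval, not a 95% one, and a directional aim does not declare a one-sided test. The paragraph needs correcting even if one-sided was intended.

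Second, the method is inferred by solving backwards, and a condensed article may leave the formula to the full protocol. Both points are fair, and the sponsor's actual method remains unknown. The issue is not an omitted detail, however. The article prints inputs and a result, and under the usual reading of its confidence level the standard two-group formula does not lead from one to the other.

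Third, a reader might infer from the 70% that the study is under-powered, or, by splitting a total of 508 into two groups of 254, that power is only about 42%. The documents support neither inference. Both need a second group that this single-cohort study does not enrol. The primary outcome is defined among the family planning users as a whole, and no county-level primary test is stated. The reference is an external 31%, against which the planned enrolment is ample.

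**Conclusion.** The stated calculation is inconsistent. With all stated adjustments, 508 matches the standard two-group formula at one-sided 5%. Under the conventional two-sided reading the same formula needs 645 per group (645 / 508 = 1.27, or 27% more), and 508 per group gives 70% power where the article states 80%. The formula also presupposes two groups in a study that has one.

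This is a fault in the sample size statement, not evidence that 1016 women are too few. For the comparison that the design can make, power is about 94% per county and above 99% overall. Those figures rest on a true rate of 21%, the stated design effect and attrition, and a reference rate treated as known. Sampling error in the survey rate would lower them. The 70% figure rests on the two-sided reading and on two groups of 508.

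**What to change.** Keep 1016 and rewrite the Sample size paragraph so that it names the sidedness, the comparison and the power that goes with them.

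- **If the comparison is the cohort against the survey rate:** state that, at two-sided 5% and treating 31% as fixed, 508 women in a county (effective 237) give about 94% power to detect 21%, and all 1016 (effective 474) give above 99%. Add that this ignores sampling error in the survey rate.
- **If a two-group contrast is kept:** say what the second group is. Then either state about 70% two-sided power with 508 per group (about 94% with 1016 per group), or declare the test one-sided at 5%, for which 80% is right with 508 per group.
- **In either case:** describe 508 as the per-county figure, not as a total.

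The cost is one rewritten paragraph and no added participants. The one drawback is that, if a two-group contrast of 508 per group is kept two-sided, the published power becomes less favourable.
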